## Background

Osteoporosis is characterized by compromised bone strength and higher fragility, resulting in an increased fracture risk [1]. The measurement of areal bone mineral density (BMD) by dual-energy X-ray absorptiometry (DXA) is the most common way to measure bone mass and to assess fracture risk. Yet, bone strength is also determined by bone geometry, bone microarchitecture, bone remodelling and intrinsic tissue quality [2]. Thus, it is not surprising that BMD only partially explains the variance of strength and fracture risk [3]. It has been postulated that markers of bone remodelling determined in blood or urine could be independent predictors of fracture risk [4]. Assessment of changes in bone microarchitecture has been limited, since bone biopsies were necessary to investigate these parameters in the past. This technique is limited to a non-weight bearing bone such as the iliac crest. Today, high-resolution peripheral quantitative computerized tomography (p-QCT) allows an efficient and quantitative evaluation of bone microarchitecture [5,6]. It determines in three dimensions true volumetric density (g/cm^3^), and can directly assess trabecular thicknesses, trabecular separations, and trabecular number, and also provides additional geometric variables such as cross-sectional area (CSA) and information on structural pattern (rod vs. plate structure) with a relatively low irradiation, high accuracy and precision [7]. P-QCT thus provides a unique non-invasive opportunity to explore the effects of diseases on bone microarchitecture and of therapies intended to halt or reverse these changes [8].

Postmenopausal bone loss and fracture risk are associated with an imbalance in bone turnover. As a therapeutic agent, calcitonin binds to specific receptors on the osteoclasts and reduces their relative hyperactivity.

The formula of nasal calcitonin is well tolerated. The most common side effects consist of mild or moderate rhinitis symptoms, such as nasal congestion and sneezing, or nasal dryness [9,10]. Rarely, hypersensitivity reactions may occur.

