### Study population

The study population will consist of 100 postmenopausal women aged 45 to 70 years with a BMD T-Score between 0.0 and -2.49. In- and exclusion criteria are detailed in Table 1. Given the possible administration of placebo treatment, women with osteoporosis are excluded from the study for ethical reasons. Study participants are being recruited through advertisements in local newspapers; recruitment has started in January 2007.

**Table 1 T1:** In- and exclusion criteria

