**Inclusion criteria**
• Women aged 45 to70 years
• Natural or surgical menopause = 1 year
• T-Score between 0.0 and -2.49 (spine or proximal femur – total or femoral neck, measured by DXA)

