#### Statistical analysis

Data will be summarized with respect to demographic and baseline characteristics, efficacy observations and measurements, and safety observations and measurements.

To assess the treatment effects of calcitonin on bone microarchitecture and provide a proof of concept, the primary analysis of the efficacy endpoints in this exploratory trial will be based on the observed data of the per-protocol population. Secondarily, an ITT analysis may be performed to test the robustness of the results.

For each analyzed parameter a two-sided t-test will be applied. The change from baseline between the two different groups (active treatment/placebo) will be compared by an analysis of covariance (ANCOVA) model with change as the response variable, the baseline value as a covariate, and treatment as a fixed factor.

The assessment of safety will be based mainly on the frequency of adverse events and on the number of laboratory values that fall outside of pre-determined ranges. Other safety data (e.g. electrocardiogram, vital signs, special tests) will be considered as appropriate.

Analysis of adverse events will be based on the safety population which includes all randomized patients who have taken at least one dose of the study drug. Adverse events will be summarized by presenting, for each treatment group, the number and percentage of patients having any adverse event, having an adverse event in each body system and having each individual adverse event. Any other information collected (e.g. severity or relatedness to study medication) will be listed as appropriate.

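### The ANCOVA for the p-QCT endpoints adjusts only for each parameter's own baseline value and leaves out pre-dose bone turnover, giving up a small amount of precision that data already collected could recover

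*Protocol article*

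**What the plan says.** Under Statistical analysis, the protocol article compares change from baseline between arms by an ANCOVA "with change as the response variable, the baseline value as a covariate, and treatment as a fixed factor". The sentence before it reads "For each analyzed parameter a two-sided t-test will be applied", a test that adjusts for nothing. No other covariate is named. Study medication gives a 1:1 allocation and mentions no stratification factor.

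The study population is "100 postmenopausal women aged 45 to 70 years". Table 1 adds "Natural or surgical menopause = 1 year"; the comparison sign seems to have been lost in text conversion, and I read it as at least one year. Neither list in Table 1 sets an upper limit on years since menopause.

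The Background says that "Postmenopausal bone loss and fracture risk are associated with an imbalance in bone turnover" and that "calcitonin binds to specific receptors on the osteoclasts and reduces their relative hyperactivity".

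Table 2 marks bone markers at screening (day -7 to -3) and at baseline (day 0), and the Laboratory test section names CTX as the resorption marker. Table 2 also marks medical history at both of these visits, without listing its contents.

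**The concern.** The outcome is a change over two years. The baseline value of a p-QCT parameter describes how much bone a woman has at entry. It does not directly describe how fast she is losing it. The article's own rationale ties loss to turnover, and eligibility admits women at very different distances from menopause, so some between-woman variation in two-year change may be predictable from pre-dose turnover. Leaving that variable out keeps the predictable part in the error term. With about 40 evaluable women per arm, a chance difference between the arms in baseline turnover also contributes to the error of the estimate. These are not two separate harms: the unadjusted standard error already contains the chance-imbalance component.

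**Working it through.** **The article's own figure.** Sample size calculation states 80 evaluable women (40 per arm), 80% power, a 3.5% difference in BV/TV, 20% drop-out and 100 enrolled. The drop-out step reproduces: 80 / (1 - 0.20) = 100. The 80 itself cannot be reproduced, because neither the SD nor alpha is given.

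**Implied SD (back-solved).** Assume two-sided alpha 0.05 and the normal approximation:

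SD = 3.5 / [(1.960 + 0.842) × √(2/40)] = 3.5 / (2.802 × 0.2236) = 5.59.

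The noncentral t version gives 5.52. I treat 5.59 as the SD remaining after adjustment for the baseline value; the article does not say whether its calculation was for the t-test or the ANCOVA. The matching standard error is 5.59 × 0.2236 = 1.25.

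**Effect of adding covariates.** Let R² be the share of that residual variance explained by pre-dose turnover, with years since menopause where available. The documents give no value, so 0.02 to 0.15 is an assumed range.

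- Standard error ratio = √(1 - R²)
- Equivalent sample size factor = 1 / (1 - R²)
- Power = Φ(2.802 / √(1 - R²) - 1.960)
- Shift from a one-standard-error imbalance = √(2/40) × √R² × 5.59, where √(2/40) = 0.22 SD of the covariate

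| R² (assumed) | SE ratio | Equivalent extra patients | Power at 40 per arm | Shift at one-SE imbalance |
|---|---|---|---|---|
| 0 | 1.000 | 0% | 80.0% | 0 |
| 0.02 | 0.990 | 2% | 80.8% | 0.18 |
| 0.05 | 0.975 | 5% | 82.0% | 0.28 |
| 0.10 | 0.949 | 11% | 84.0% | 0.40 |
| 0.15 | 0.922 | 18% | 86.0% | 0.48 |

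Shifts are on the same scale as the 3.5 targeted.

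**What the table leaves out.** The power formula ignores the price of the covariates. With 80 women, the stated ANCOVA leaves 80 - 3 = 77 residual degrees of freedom. Each added covariate raises the variance of the treatment estimate by about 1/77 = 1.3% on average, through chance correlation with treatment. At R² = 0.02 the net variance factor is therefore about 0.98 × 1.013 = 0.993 with one covariate, and about 0.98 × 1.026 = 1.005 with two. At the bottom of the range the gain is essentially nil. At R² = 0.15 with one covariate the factor is 0.85 × 1.013 = 0.861, so most of the gain remains.

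**Check that the stated model is valid.** In a simulation of 8,000 trials per setting, omitting a prognostic covariate left type I error near nominal (4.9% at R² 0.10; 5.4% at R² 0.30, a value beyond the range used here). The mean estimate under a true difference of 3.5 was 3.50 and 3.49. At R² 0.10, simulated power was 78.3% with the covariate omitted and 82.0% with it included. The simulated baseline is slightly below 80% because 5.59 comes from the normal approximation while the simulation uses the t distribution.

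**The case against.** The strongest reply is that nothing here is an error. ANCOVA on change with the baseline value is a standard model, the trial calls itself exploratory, and further covariates often belong in an analysis plan that is not shown. The validity part stands in full. The deferral part is weaker, because the article does not leave the model open: it names the response, the covariate and the factor.

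Several stronger readings are tempting, and the documents do not support them.

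- **Bias or inflated type I error.** Neither follows under randomisation, and the simulation shows neither. The per-protocol primary analysis weakens the protection that randomisation gives, but that is a separate matter and added covariates would not repair it.
- **Imbalance passing straight into the estimate.** It enters only through the covariate's coefficient, which is why the shifts above are fractions of a point.
- **Years since menopause as an established marker of rate of loss.** The Background supports turnover, and only as an association. It says nothing on menopausal age, and a span of two or more decades is inferred from the upper age of 70.
- **A menopause date already on file.** The inclusion criterion needs only a threshold of about one year, and Table 2 lists medical history without detail.
- **Heterogeneity left wholly unhandled.** The T-score, BMI, disease and prior-treatment criteria narrow the population, all women receive calcium and vitamin D unless they do not tolerate it, and the concurrent placebo arm absorbs the natural course in expectation.
- **A drug effect that differs by turnover.** That is effect modification; main-effect covariates do not address it.

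**Conclusion.** The point holds as a minor matter of efficiency. The model as published is valid, but it leaves out a pre-dose variable that the article's own rationale links to bone loss and that the schedule already collects. The likely gain is from about 81% to 86% power in place of 80%, before the small cost of the covariates, and about nothing if they explain only 2% of the residual variance. A one-standard-error imbalance in the covariate corresponds to about 0.2 to 0.5 points against 3.5.

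These figures rest on an assumed two-sided alpha of 0.05, an SD of about 5.5 to 5.6 back-solved from the stated sample size, and an assumed R² of 0.02 to 0.15. None of the three is in the document. The support is firmer for baseline CTX than for years since menopause.

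**What to change.** In Statistical analysis, before unblinding, prespecify the ANCOVA for each p-QCT parameter as change on treatment, baseline value of that parameter and log pre-dose CTX. State which sample supplies the CTX value, since Table 2 marks bone markers at both screening and baseline, and require that it was drawn before the first dose. Add years since menopause only if the date is recorded in the medical history, with a simple stated rule for uncertain dates. Use no post-baseline marker as a covariate, because treatment may already have altered it.

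The cost is one sentence and one or two of about 77 residual degrees of freedom. CTX needs no new visit or assay. If the covariates prove uninformative, the variance of the treatment estimate rises by about 1.3% for each, which is negligible.

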## Summary

This study will investigate the effects of nasal salmon calcitonin on bone microarchitecture and its relation with markers of bone turnover in postmenopausal women. It should thus give a new insight into the specific effects of calcitonin on different bone parameters.
